**15. Statistical Considerations**

The randomized clinical trial study design uses a rigorous methodology to evaluate the clinical research questions posed in this proposal. The sample size has been calculated based on estimates from previous published data results and will ensure adequate statistical power while maintaining efficiency. Minimal loss to follow-up is expected (<10%). The primary analyses will be conducted excluding patients with missing outcomes. Intention-to-treat analysis will also be performed (ie. including all patients randomized).

Descriptive statistics (means  $\pm$  standard deviation (SD), proportions and, when required, medians and interquartile ranges) will be performed to compare socio-demographic, clinical and epidemiological characteristics of patients at baseline between experimental and control groups. These characteristics include: age, sex, region of residency and education/occupation, among others. Proportions of patients cured at each of the follow up dates will be assessed. Proportions will be compared between the two groups using chi-square tests. Means derived from continuous variables will be compared using t tests or non-parametric tests, as appropriate.

Time-to-cure will be compared between the two groups using Kaplan-Meier curves and crude rates of cure will be calculated by person-years. For comparison purposes, we will assume that cure occurred at the time of the visit for cured patients. In a randomized clinical trial, we expect to find no differences in patient characteristics

between the two groups. However, when sample sizes are small, it will likely be necessary to adjust for slight imbalances in independent variables between the two groups. Cox proportional-hazard models will be constructed to determine the effect of treatment on time-to-cure, adjusting for patients' baseline characteristics. Results will be expressed in terms of hazard ratios and 95% confidence intervals. The proportional hazard assumption will be examined using graphical methods and the proportional hazard test in SAS PHGLM. Secondary analyses will be conducted in a similar manner, assuming that all those who were lost to follow-up were cured only at the end of the 12 month follow-up period.

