Assuming a constant hazard ratio over time, with a sample size of 40 subjects in each of the two intervention groups (total of 80 subjects), the log-rank test for equality of survival curves will have 80% power to detect a statistically significant difference in proportions cured between the two groups based on a difference in cure proportions of at least 32% (hazard ratio of 2.6, proportion cured in the control group of 35% and proportion cured in the treated group of 67% - (less than the 72% observed at 3 months in our previous trial). If the proportion cured in the experimental group is higher than 67%, then this will increase the statistical power of the test. We believe that this will provide sufficient and compelling evidence for policy-makers.

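### The secondary analyses count every patient lost to follow-up as cured at month 12, so cure is assigned without being observed and the adverse direction is never tested

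*Protocol*

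**What the plan says.** Section 15 of the protocol names three treatments of patients without a month-12 outcome.

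- Primary: "The primary analyses will be conducted excluding patients with missing outcomes".
- Intention-to-treat: "Intention-to-treat analysis will also be performed (ie. including all patients randomized". No value is given for a missing outcome.
- Secondary, directly after the Cox models for time-to-cure: the same kind of analysis, "assuming that all those who were lost to follow-up were cured only at the end of the 12 month follow-up period".

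The third is the only place where a lost patient is given an outcome, and the outcome is success. Section 15 expects loss below 10%. Section 8.7 reserves cure for lesions that have reached Stage M4. It lists as failure Stage M0 at month 1, Stage M1 at month 3, a return to a lower stage, or a new lesion.

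**The concern.** A secondary analysis of this kind is normally read as a check on whether missing patients could have changed the answer. Here it supplies a cure that nobody saw. The rule covers all lost patients without exception, so someone classed as a failure at month 1 or 3 who then stops attending becomes a success at month 12. That conflicts with section 8.7.

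The rule also leaves a gap. The primary analysis drops these patients, the intention-to-treat analysis does not say what becomes of them, and the secondary analyses make them cures. A reader who wants to know whether the result survives if lost patients were not cured finds no analysis that explicitly answers it. For some splits of the losses, the secondary result would be more favourable than the primary.

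**Working it through.** **Inputs from the protocol.** 40 patients per group; cure proportions 35% and 67%; hazard ratio 2.6; 80% power; loss below 10%, so at most 7 of 80 (8 of 80 is exactly 10%). **Assumptions.** Two-sided 0.05, the split of losses between arms, and the timing of cures.

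**The plan's own figure.** HR = ln(1 − 0.67)/ln(1 − 0.35) = 2.574, which rounds to 2.6. Expected events = 80 × (0.35 + 0.67)/2 = 40.8. Freedman's log-rank formula gives z = √40.8 × (2.574 − 1)/(2.574 + 1) − 1.96 = 0.85, so power is 80.3%. The stated 80% reproduces, and 35% and 67% are used below as the design case.

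**Effect on the month-12 proportion.** If a fraction f of an arm is lost and p is the cure proportion among those observed, the rule turns p into p + f(1 − p), and counting lost patients as not cured turns it into p − fp. Relative to exclusion (E = imiquimod, C = control):

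- the rule changes the difference by f_E(1 − p_E) − f_C(1 − p_C). At 67% and 35% this is positive only if imiquimod loses more than 0.65/0.33 = 1.97 times as many patients as control;
- counting lost patients as not cured changes it by f_C·p_C − f_E·p_E. This is positive only if control loses more than 0.67/0.35 = 1.91 times as many as imiquimod.

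**Examples** (uncorrected chi-square). The first two fix 23 versus 14 observed cures and lose 7 of 80. The third takes 67% and 35% of the 36 observed per arm and loses 8 of 80, the edge of the expectation.

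| Lost, imiquimod v control | Excluded | Protocol rule | Not cured | Adverse case |
|---|---|---|---|---|
| 6 v 1 | 23/34 v 14/39: +31.7 (p = 0.007) | 29/40 v 15/40: +35.0 (p = 0.002) | 23/40 v 14/40: +22.5 (p = 0.044) | 23/40 v 15/40: +20.0 (p = 0.073) |
| 1 v 6 | 23/39 v 14/34: +17.8 (p = 0.13) | 24/40 v 20/40: +10.0 (p = 0.37) | 23/40 v 14/40: +22.5 (p = 0.044) | 23/40 v 20/40: +7.5 (p = 0.50) |
| 4 v 4 | 67.0% v 35.0%: +32.0 | 70.3% v 41.5%: +28.8 | 60.3% v 31.5%: +28.8 | 60.3% v 41.5%: +18.8 |

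The adverse case counts lost imiquimod patients as not cured and lost control patients as cured.

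**Effect on the hazard ratio.** Cox models with Efron ties were fitted to the 23 versus 14 cures. Early timing: 10, 8, 5 versus 6, 5, 3 cures at months 1, 2, 3. Spread timing: 5, 5, 5, 4, 2, 2 versus 3, 3, 3, 2, 2, 1 at months 1, 2, 3, 6, 9, 12. For the not-cured column, lost patients stay at risk to month 12 with no event.

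| Lost | Timing | Excluded | Protocol rule | Not cured |
|---|---|---|---|---|
| 6 v 1 | early | 2.42 | 2.44 | 1.94 |
| 6 v 1 | spread | 2.43 | 2.46 | 1.94 |
| 1 v 6 | early | 1.64 | 1.45 | 1.94 |
| 1 v 6 | spread | 1.65 | 1.44 | 1.94 |

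A simulation on the protocol's visit schedule, with exponential cure times and loss unrelated to outcome, shows how much timing matters:

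- 35% and 67% reached by month 12: the median HR moves from 2.65 (excluded) to 2.89 (rule) with 8 v 0 lost, and from 2.59 to 2.31 with 4 v 4 lost.
- 35% and 67% already reached by month 3: it moves from 2.62 to 1.69 with 8 v 0 lost, and from 2.63 to 3.36 with 0 v 8 lost.

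**The case against.** The best defence is that the rule was meant to be cautious. It gives the latest possible cure date, and for a lost patient who really was cured that understates the speed of cure. It also sits with the time-to-cure models, where the hazard ratio barely moves in the 6 versus 1 example. It governs a secondary analysis with loss expected below 10%, and the plan also names exclusion and an intention-to-treat analysis whose handling of missing outcomes may be set in a statistical analysis plan. All of that stands, and it limits the importance of the point. It does not rescue the rule: a late date says nothing about whether cure occurred, and the rule is written in the protocol, not left for later.

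Stronger readings are tempting but are not supported:

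- *That the rule always favours imiquimod.* Equal losses shrink the difference, losses on control shrink it further, and with early cures losses on imiquimod lower the hazard ratio. Early cure is not remote, since section 15 cites a month-3 cure figure from the previous trial.
- *That it manufactures an effect where there is none.* With 14 cures in each arm and 6 versus 1 lost, the rule gives 20/40 versus 15/40, or +12.5 points. That example is null only if no lost patient was cured; among those observed the difference is already 14/34 versus 14/39, or +5.3. The +12.5 has p = 0.26.
- *That patients withdrawn for worsening become cures.* Section 11 allows such withdrawals, but the protocol does not say whether they count as lost to follow-up.
- *That counting lost patients as not cured is the safe choice.* With 1 versus 6 lost it gives +22.5 against +17.8 with lost patients excluded.

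**Conclusion.** The point holds as a fault in a stated rule. The secondary analyses assign cure to patients in whom it was not observed, against section 8.7, and no stated analysis explicitly takes them as not cured. A reader might infer a systematic bias towards imiquimod; the figures show only that the direction depends on which arm loses more and on when cures occur. Within the protocol's own loss expectation, the 6 versus 1 split puts the rule 3.3 points above exclusion and the 1 versus 6 split puts it 7.8 points below. The gap between the rule and the not-cured reading is 12.5 points in either direction. These sizes rest on assumed splits, cure counts and timings, and the p-values are read against an assumed two-sided 0.05. The primary analysis and the sample size are untouched. The rule should be corrected, but it is not a reason to hold the trial.

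**What to change.** Replace the last sentence of the time-to-cure paragraph in section 15 with two required sensitivity analyses.

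1. Patients lost to follow-up without an observed Stage M4 are analysed as not cured: no cure event, kept at risk to month 12 in the time-to-cure models, and counted as not cured in the 12-month proportion.
2. The adverse case is reported beside it: lost imiquimod patients not cured, lost control patients cured. It must be required, because the first analysis alone flatters imiquimod when losses fall mainly on control. In the examples above the adverse case is the lowest of the four estimates each time (+20.0, +7.5 and +18.8 points).

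The cost is a rewritten sentence, with no change to the sample size, visits or primary analysis. The downside is that the sensitivity estimates may be less favourable: in the 6 versus 1 example the adverse case gives p = 0.073 where exclusion gives 0.007.

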## **16. Administrative Procedures**

### **16.1 Ethics Review Board Approval**

The experimental protocol for this study has been designed in accordance with the general ethical principles outlined in the Declaration of Helsinki, 2000 and ICH guidelines for Good Clinical Practice( International Committee for Harmonisation) This protocol will be reviewed by the Ethics Review Board (ERB) of UPCH, McGill University, The National Institute of Health in Peru (INS-Peru), and the local IRB for areas where the patients will be treated.

The investigators will be responsible for preparing documents for submission to government and ERBs and obtaining written approval for this study. All approvals will be obtained prior to the initiation of the study.

### **16.2 Informed Consent**

The informed consent form will be in Spanish, the patient's native language (Appendix 2). The Investigator or his/her staff will explain the nature of the investigation and the risks involved to each patient prior to enrollment, and will obtain written informed consent. The patient will also be informed that he/she is free to voluntarily withdraw from the study at any time. The patients will be provided with an information sheet which will summarize the nature of the trial.

### **16.3 Study Monitoring**

The investigators will allow representatives of DNDi and the study monitor to periodically monitor the study, all CRFs and corresponding source documents for each patient will be made available. It is important that the investigators and other trial site staff are available at these visits. The monitoring visits provide DNDi with the opportunity to evaluate the progress of the study, verify the accuracy and completeness of CRFs, resolve any inconsistencies in the study records, as well as to ensure that all protocol requirements, applicable regulations, and investigator's obligations are being fulfilled. The investigators must maintain source documents such as laboratory and consultation reports, history and physical examination reports, etc., for possible review. The Principal Investigator will record the date of each visit together with a summary of the status and progress of the study. Proposed actions will be confirmed in writing. The investigators will allow audit of the trial by any external regulatory agency to verify data submitted.

**16.4 Modification of Protocol**

No deviations from the protocol may be made. The investigators may approve minor exceptions on a case-by-case basis. If modification of the protocol is necessary, the modification must be initiated and confirmed in writing by the investigators and approved by the ERB prior to implementation.

**16.5 Departure from Protocol**

If an emergency occurs that requires a departure from the protocol for an individual, the departure will only be for that individual. The physician in attendance in such a situation will, if circumstances and time permit, contact the Principal Investigators ([name] in Lima and [name] in Montreal) immediately by telephone. The CRF will detail the departure from the protocol and state the reasons for such departure. ERBs must be notified immediately if the departure from the protocol affects the safety or rights of the patient.

**16.6 Suspension of Study**

If safety concerns arise during the study, the ERBs may recommend to the investigators that the study be suspended, amended or terminated. The study may be suspended until the situation or safety concern has been resolved.

### **16.8 Record Retention**

The investigators shall retain the clinical study records until such time as directed by DNDi, UPOCH and McGill University. Records are to be retained for at least 10 years after regulatory approval or if not approved, until 10 years following the completion of the trial including follow-up.

### **16.9 Study Insurance**

Insurance for the study will be purchased. The maximum limit of indemnity per person insured shall be \$1,000,000. This insurance can be purchased from for example HDI, Munchen, Germany. However, the insurance company to be used for this study has yet to be identified.

